**Figure 2 figure2:**
[figure not shown]
Schedule of enrollment, interventions, and assessments. Adopted from SPIRIT (2013).
-t1: prior to treatment; t1: posttreatment; t2: 3 months posttreatment; t3: 6 months posttreatment; t4: 12 months posttreatment; PDI: pain disability index; IPQ-K (DLV): Dutch language version of the Illness Perception Questionnaire; PSEQ: Pain Self-Efficacy Questionnaire; NRS: numeric rating scale; SF12: 12-item short-form health survey; GPE: global perceived effect.

#### Primary Outcome

Self-perceived pain disability will be measured with the Pain Disability Index (PDI) [34]. This questionnaire consists of 7 items ranging from 1 (no disability) to 10 (maximum disability). Each item relates to the self-reported disability in the context of family/home, recreation, social, occupation, sexual, self-care, and life support. The PDI score (0-70) is obtained by summing all individual items. The PDI score is evaluated as responsive, with a change of 8.5 to 9.5 points considered to be clinically important [35].

#### Secondary Outcomes

##### iMTA Medical Cost Questionnaire

The iMTA Medical Cost Questionnaire (iMTQ) measures all health care costs that have been made during a specific period [36]. The questionnaire contains 18 items that refer to 11 primary care components (eg, medication use, general practitioner visits) and 5 secondary care components (eg, hospital visits). Two optional questions will be added that relate to informal care by relatives and health care–related travel expenses. Furthermore, we will add two questions from the iMTA Productivity Cost Questionnaire (iPCQ) to acquire an indication of the productivity losses, as the number of hours work lost due to the disease [37,38].

##### Twelve-Item Short Form Health Survey

The 12-item short-form health survey (SF-12) contains 12 multiple choice items that cover 8 health status domains. Raw item scores are combined and transformed into two summary scores: a physical and a mental component score [39]. Higher scores reflect better mental or physical functioning. The SF-12 is considered valid and reliable and has been previously used in patients with chronic pain [40-43].

##### Pain Self-Efficacy Questionnaire

The Pain Self-Efficacy Questionnaire (PSEQ) assesses self-efficacy beliefs regarding daily life goals in the context of chronic pain [44,45]. The questionnaire includes 10 items that ask a patient to indicate the degree of confidence to perform specific activities (eg, socializing with friends) despite the pain. Responses are obtained using a Likert scale, ranging from 0 (not confident at all) to 6 (completely confident). The sum of individual scores indicates the total pain self-efficacy. A study on the psychometric properties in a Dutch population of patients with chronic pain demonstrated that the PSEQ is an internally consistent unidimensional instrument [46].

##### Brief Illness Perceptions Questionnaire Dutch Language Versions

The Dutch language version of the Illness Perception Questionnaire (IPQ-K [DLV]) measures how patients evaluate their current health condition with respect to 8 areas of cognitive perception [47]. The questionnaire includes 9 items, with 8 items covering a different cognitive area (eg, controllability) with a Likert-scale response option, ranging from 0 (absolutely no control) to 10 (extreme amount of control). The last item requires the patient to list the 3 most important causes for their current condition. A systematic review on the clinimetric properties of the IPQ-K (DLV) concluded that the questionnaire is appropriate to explore the illness beliefs of various patient groups, including acceptable test-retest reliability. However, the smallest detectable change of 42 (on a maximum of 80 points) implies that the use of an IPQ sum score to detect individual changes is not recommended [48]. Therefore, we will not use the sum score but instead evaluate each item separately [49].

##### Pain Intensity

We will measure current pain intensity on a numerical rating scale ranging from 0 (no pain) to 10 (worst pain imaginable).

##### Global Perceived Effect

The global perceived effect (GPE) evaluates to what extent the patient’s current condition has improved or worsened compared to the period prior to the treatment program. Patients respond with a 5-point Likert scale, ranging from 1 (very much improved) to 5 (very much worsened). The psychometric properties of this questionnaire have been tested in the context of various musculoskeletal disorders and are considered adequate [50].

##### System Usability Scale

The system usability scale is a 10-item questionnaire that is frequently used for evaluation of the perceived usability of software apps [51,52]. Each item is scored on a range from strongly disagree (1) to strongly agree (5). The total usability score is expressed on a 0-100 scale with higher scores indicating more usability.

##### System Usage Data

To obtain insight into the frequency, intensity, and duration of engagement, we will obtain the following system usage data for each time point: average number of logins per week, average number of features accessed per login, average minutes spent with the app at each login, total time spent with the app per week, number of Insight Cards created, number of value-based goals created, and number of steps created within the Value-Based Goals module**.**

##### Intervention Reporting

We will ask each center to provide a detailed overview of their intervention according to the Template for Intervention Description and Replication checklist [53]. This checklist aims to provide a set of items to describe an intervention for enhancing understanding and replication. Although the interdisciplinary interventions are not the main focus of this study, we will use this intervention to provide an indication of between-center heterogeneity and to assess to what extent the interventions will be modified during the study (item 10).

### Harm

We do not expect any serious adverse events as a result of using the app. However, we will monitor any negative consequence that results from usage. During the training of the treatment team, we will instruct the health care providers to report negative experiences of the app (eg, frustration due to low digital literacy skills). During biweekly contact with treatment teams, the researcher will also actively ask for any adverse event. In the unlikely event of harm, patients can appeal to the liability insurance of the sponsor that covers any damage to research subjects caused by the study within 4 years after the end of the study.

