**Methods:**

We will perform a multicenter randomized controlled trial with two parallel groups. Within the 12-month inclusion period, we plan to recruit 158 adult patients with chronic pain during the initial stage of their interdisciplinary treatment program in one of the 6 participating centers. Participants will be randomly assigned to the standard treatment condition or to the enhanced treatment condition in which they will receive the AGRIPPA app. Patients will be monitored from the start of the treatment program until 12 months posttreatment. In our primary analysis, we will evaluate the difference over time of pain-related disability between the two conditions. Other outcome measures will include health-related quality of life, illness perceptions, pain self-efficacy, app system usage data, productivity loss, and health care expenses.

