#### Health Care Providers

To qualify for participation, treatment teams will be required to attend a workshop where they will receive instruction on how to adhere to the study protocol and how to use the app. In addition, health care providers will be instructed to document notable or unexpected events and to participate in a focus group after the study period. Each treatment location is also required to provide a research assistant who is not involved with the treatment program. This research assistant will be responsible for performing the treatment allocation procedure.

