#### Adherence to the Intervention Protocol

The app will be made available to the members of the treatment teams to become accustomed to the content. The training will be provided by two researchers ([name]) and include an overview of the purpose and rationale of the study, as well as detailed instructions on how to use the app within the context of the treatment program. This includes identifying an appropriate moment within the treatment program to introduce the app, determining which member of the team will be responsible for the introduction and encouragement to regularly evaluate the app content, and provide feedback to the participant. During the study, a researcher will have biweekly contact with the treatment team to obtain feedback and discuss progress. Furthermore, two audit sessions will be planned at each location. The researcher will schedule an appointment to discuss overall progress, protocol adherence, and to share examples of good practice with the treatment team. During these sessions, the researcher will also inquire about substantial deviations from the protocol or discontinuation of the app during treatment.

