### Participant Timeline

Patient eligibility screening, informed consent, and treatment allocation procedures, as well as the baseline assessment, will be completed prior to the start of the treatment program. Patients in the enhanced treatment condition will receive instruction on how to download and use the app, and both strategies will be explained by a member of the treatment staff. To match the existing treatment content and procedures, the moment that the app will be introduced to patients can vary between locations. During the treatment phase, the app is considered a supplement to the main treatment activities and patients are free to decide how and when to use the app. Health care providers will be instructed to encourage and facilitate using the strategies when they expect it will reinforce the treatment process. However, both strategies can largely be used independently of any treatment activity and are expected to minimally affect direct treatment time. A member of the research team will be available to the treatment staff throughout the experimental phase for additional questions, support, and discussions regarding optimal use. Following treatment, there will be no additional monitoring in the enhanced treatment condition. Patients will continue to be able to use the app at their discretion. Posttreatment data will be obtained directly posttreatment (t1), and at 3 months (t2), 6 months (t3), and 12 months (t4) posttreatment.

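### The Harm section promises to monitor every negative consequence of app use, but its active routes run through the treatment team, so app-attributed negative experience after discharge is likely to be missed

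*Protocol article*

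**What the plan says.** The Harm section of the protocol article expects no serious adverse events from the app, but adds: "However, we will monitor any negative consequence that results from usage". It gives no end date for this. Two active routes follow. At team training, "we will instruct the health care providers to report negative experiences of the app". The second is a standing question to the teams: "During biweekly contact with treatment teams, the researcher will also actively ask for any adverse event".

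Two other sections add related duties. Under Health Care Providers, "health care providers will be instructed to document notable or unexpected events". Under Adherence to the Intervention Protocol there are two audit sessions per location with the treatment team, at which "the researcher will also inquire about substantial deviations from the protocol or discontinuation of the app during treatment".

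On the period after discharge, Participant Timeline says: "Following treatment, there will be no additional monitoring in the enhanced treatment condition". It goes on: "Patients will continue to be able to use the app at their discretion". The Methods paragraph of the abstract sets the horizon: "Patients will be monitored from the start of the treatment program until 12 months posttreatment".

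**The concern.** The app is meant to prevent relapse, and the first hypothesis is about keeping treatment gains after the program ends. The posttreatment year is therefore when its benefits and its drawbacks matter most. It is also when the people named as reporters of harm would normally have stopped seeing the patient.

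If the plan is followed as described, the final report could show few or no negative experiences with the app during follow-up. A reader could not tell whether there were none or whether nobody asked. The article says the results will guide decisions on clinical uptake, so the difference matters, even for a low-risk intervention.

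**Working it through.** The check sets what is promised beside what is collected. The plan gives no figure to reproduce.

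1. **Who is asked about harm, and when.**
   - Provider reports (Harm): the informant is the provider. They depend on the provider being in contact with the patient.
   - Biweekly questions (Harm): the informant is the treatment team. The contact is described as running during the study, so it may continue while some patients are in follow-up. The article does not describe the teams as seeing discharged patients.
   - Documentation of unexpected events and the focus group after the study period (Health Care Providers): the informant is again the provider.
   - Audit sessions (Adherence to the Intervention Protocol): the informant is the team, and the question on stopping the app is limited to the treatment period.

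   All four go through the treatment team.

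2. **What patients are asked directly.** Table 1 and the outcome sections list the PDI, GPE, SF-12, medical cost and productivity questions, illness perceptions, pain self-efficacy, pain intensity, the system usability scale and app usage data. Several would register a patient getting worse. None is described as asking whether the app caused a negative experience. The usability scale comes closest, but it is described as a 0 to 100 score of perceived usability. Data Management names three electronic sources (routine questionnaires, additional surveys and app usage data) and describes none of them as carrying harm reports.

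3. **What patients can volunteer.** Recruitment offers an independent counselor by email, for questions and support, throughout the study. The patient has to take the first step, and the article does not present this as a route for reporting harm.

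4. **Size of the period concerned.** Planned sample 158 (abstract), allocation 1:1 (Design), follow-up 12 months after treatment:
   - app arm: 158 / 2 = 79 patients;
   - posttreatment access: 79 × 1 year = 79 patient-years before attrition.

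   The figure is approximate, because simple randomization and randomization by treatment group need not give an exact half. It measures access, not use; the protocol itself expects logins to decline.

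5. **Where a patient item could be placed.** Table 1 puts the GPE in the additional electronic survey and uses it at t1. Cost Effectiveness places the SF-12, medical cost and productivity questions at 3 and 6 months. The visible text does not confirm a study-run survey at 12 months, since the PDI comes through the centers' routine system. The schedule figure is not shown.

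**The case against.** Three stronger readings are tempting, and the article does not support them.

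- **That Participant Timeline ends harm reporting at discharge and so contradicts the Harm section.** The sentence on no additional monitoring stands in a paragraph about introducing and supporting the app. The same paragraph goes on to list data collection after treatment. It can simply mean that the app arm gets no extra contact beyond what both arms get. The abstract says that patients are monitored to 12 months.
- **That harm in follow-up would go entirely unseen.** The PDI to 12 months, and the SF-12 and health care use at 3 and 6 months, allow a comparison of worsening between randomized arms. So does the GPE where it is collected, since it asks directly about improvement or worsening. Patients can also write to the counselor.
- **That a stated share of app-access time lacks an active assessor.** Program length is not given, so any percentage would only reflect an assumed length.

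There are two further objections. First, an article condenses its protocol, and item wording or adverse-event forms may be in the full document. That is fair, and for this reason the point is confined to the routes the article itself describes, set against its own open-ended promise. Second, the authors say they deliberately added few measures in order to limit burden, and the app carries little risk. Both lower the priority.

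What survives is narrow. The outcome scales can show that one arm did worse, but they cannot attribute an experience to the app. They are also not described as asking about the article's own example of harm, frustration linked to low digital literacy.

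**Conclusion.** The point holds in a limited form. The undertaking covers any negative consequence of use, while the active routes described depend on a treatment team not described as seeing patients after discharge. No listed questionnaire is described as asking patients about negative effects of the app. App-attributed negative experience is therefore likely to be missed during the 12 months of posttreatment use, about 79 patient-years of access before attrition. General worsening would not be missed.

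This rests on two assumptions: that teams do not routinely see patients after the program, which the article leaves open, and that the unseen full protocol has no patient item on harm. If either is wrong, a clarifying sentence in the Harm section is enough. The effect on the primary analysis is nil. The effect is on what the trial can say about harms in follow-up, and the point is worth correcting because the remedy is cheap.

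**What to change.** - Add one patient-reported item on negative experiences (yes/no with free text), worded identically in both arms, to the additional electronic surveys at t1, 3 months and 6 months. Include it at 12 months if a study survey is sent then; otherwise use a short separate send.
- Add an app-specific follow-up question for app users.
- Summarize the answers by arm and time point, with the number of patients asked. Patients are not masked, so the comparison should be read descriptively.
- State in the Harm section that provider reports cover the treatment phase and patient reports cover follow-up.
- If the item is not added, limit the promise, and any conclusion on harms, to the treatment phase.

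The cost is a slight increase in patient burden, possibly one extra send at 12 months, and some reading of free text. A researcher already monitors incoming data. With 88 patients recruited by March 20, 2020, some may already have passed a time point and will lack the item there; the report should say so.

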### Data Analysis

During all analyses, the treatment condition will be masked to the researchers. We will analyze the data according to the intention-to-treat principle and include patients in the analysis regardless of their adherence to the treatment protocol. We will perform no interim analysis. We will collect data at the following time points: –t_1_ (baseline), t_1_ (immediately postintervention), t_2_ (3 months postintervention), t_3_ (6 months postintervention), and t_4_ (12 months postintervention). Prior to the main analysis, we will check the randomization by examining the distribution of baseline characteristics between both groups.

#### Sample Size Calculation

The sample size calculation is based on a 2-factor repeated-measures analysis of variance with within-factor time (5 levels) and between-factor treatment (2 levels) conditions on the outcome variable PDI. We have set the α to .05, the power (1 – β) to .95, and assumed a moderate treatment effect (*f*=0.2). To account for the expected dependencies of patients within each of the 5 participating treatment locations, we applied the Donner et al [55] formula for the variance inflation factor, assuming an intracorrelation coefficient of 0.2 [56,57]. Furthermore, we corrected the analysis for an expected attrition of 20%, which is based on the average attrition of similar studies that used the PDI [21,58,59]. Based on these calculations, a minimum sample size of 157 participants, equally divided over 5 treatment locations, will be required.

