### Study Setting

Six treatment facilities that provide IMPT programs participate in this study (2 hospital units and 4 rehabilitation clinics). All locations provide an interdisciplinary biopsychosocial-oriented treatment program to patients within the region, leading to a mixed rural and urban population throughout the Netherlands (ie, Arnhem, Eindhoven, Hoensbroek, Roermond, Maastricht, and Wijk aan Zee).

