### Outcomes

All six treatment facilities routinely collect outcome data with an electronic survey to monitor their patients [33]. All demographics, baseline measurements, as well as the primary outcome will be obtained by this procedure. Any outcome measures that are not part of the routine assessment will be obtained through an additional electronic survey. Table 1 includes an overview of all outcome domains, measures, and planned analysis methods. The participant flow that is depicted in Figure 2 includes all time points of data collection in this study. A researcher who is not involved with the treatment program will monitor all incoming data and will promote study retention using email reminders after 7 days and telephone reminders at 15 and 21 days postmeasurement.

**Table 1 table1:** Planned outcome domains, outcome measures, and statistical methods.

Outcome		Hypothesis/research question	Outcome measure	Method of analysis

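### The sample size is calculated for five treatment locations although six take part, so the stated minimum of 157 does not follow from the design described (a conservative error).

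*Protocol article*

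**What the plan says.** The Sample Size Calculation section uses five locations twice. It adjusts for the "expected dependencies of patients within each of the 5 participating treatment locations", and it concludes that "a minimum sample size of 157 participants, equally divided over 5 treatment locations, will be required".

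Three other places give six. The Abstract (Methods) says that patients are recruited "in one of the 6 participating centers". Study Setting says "Six treatment facilities that provide IMPT programs participate in this study", splits them into two hospital units and four rehabilitation clinics, and lists six towns. Outcomes says "All six treatment facilities routinely collect outcome data".

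The Abstract also gives the recruitment target: "we plan to recruit 158 adult patients with chronic pain". No section says that a centre joined after the calculation, is held in reserve, or is left out of the calculation or the analysis.

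**The concern.** The number of locations is more than descriptive here. For a given total it fixes the number of patients per location, and through that the VIF. If five was a real input, the published minimum answers a different question from the one posed by the six-site design in the same article. It cannot then be reproduced from that design.

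There is also a question for the analysis. The Primary Analysis section puts treatment location in the model and makes it the third level of the hierarchy. A reader should not have to guess whether five or six locations are analysed.

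**Working it through.** **Inputs stated in Sample Size Calculation:** repeated-measures ANOVA with 5 time points and 2 groups, alpha 0.05, power 0.95, f = 0.2, intracluster correlation 0.2, attrition 20%, 5 locations, result 157. **Stated elsewhere:** 6 locations; recruitment of 158.

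**Assumptions, not stated in the article:**
- the test is the time-by-treatment interaction;
- the correlation between repeated measures is rho = 0.5, with sphericity;
- the VIF is 1 + (m - 1) x 0.2, where m is the uninflated sample divided by the number of locations;
- attrition is applied as a multiplication by 1.2 (division by 0.8 is shown as the alternative).

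**Step 1, base sample.** Noncentral F test with lambda = N x 5 x f^2 / (1 - rho) and degrees of freedom 4 and 4(N - 2). At N = 48, lambda = 48 x 5 x 0.04 / 0.5 = 19.2 and power is 0.952. At N = 46 power is 0.942. The smallest sample with equal groups is therefore 48.

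**Steps 2 and 3, inflation and attrition.**

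| | 5 locations | 6 locations |
|---|---|---|
| m | 48/5 = 9.6 | 48/6 = 8 |
| VIF | 1 + 8.6 x 0.2 = 2.72 | 1 + 7 x 0.2 = 2.40 |
| Inflated N | 48 x 2.72 = 130.56 | 48 x 2.40 = 115.2 |
| x 1.2 | 156.7, so **157** | 138.2, so **139** |
| / 0.8 | 163.2, so 164 | 144.0, so 144 |

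The five-location column with x 1.2 gives the published figure. With six locations the same steps give 18 fewer patients (157 - 139; 18/157 = 11.5%).

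**Step 4, power with the planned number over six locations.** With 157 patients and VIF 2.40, 157/1.2/2.40 = 54.5 effective patients, power 0.974. With 20% lost, 157 x 0.8/2.40 = 52.3, power 0.968. If instead the uninflated sample is solved so that the whole chain returns 157, it is 51.8 (x 1.2) or 50.5 (/ 0.8), with power 0.966 or 0.962. For 158 the four values run from 0.962 to 0.975. All are above 0.95.

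**Step 5, dependence on the assumed correlation.** The base sample is 96 at rho = 0, 76 at 0.2, 48 at 0.5 and 30 at 0.7. With attrition as x 1.2:

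| rho | 5 locations | 6 locations |
|---|---|---|
| 0 | 96 x 4.64 x 1.2 = 534.5, so 535 | 96 x 4.00 x 1.2 = 460.8, so 461 |
| 0.2 | 76 x 3.84 x 1.2 = 350.2, so 351 | 76 x 3.333 x 1.2 = 304 |
| 0.5 | 157 | 139 |
| 0.7 | 30 x 2.00 x 1.2 = 72 | 30 x 1.80 x 1.2 = 64.8, so 65 |

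Six locations always need fewer patients than five. Of these four correlations, only 0.5 returns 157.

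**The case against.** The best defence is that the discrepancy does no harm. More locations mean smaller clusters and less inflation, so a minimum derived for five is more than enough for six. The article calls 157 a minimum and plans 158. This stands, and it decides the severity.

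A second defence is that the base sample of 48, the correlation of 0.5 and the x 1.2 convention are inferred. This also stands: 139 and the power figures are reconstructions. The contradiction in the text does not depend on them, and neither does the direction of the change. The match at 157 makes it very likely that five entered the calculation and is not just a slip in the prose.

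A third is that equal division over five sites is a planning simplification. That is fair. 157/5 = 31.4 is not a whole number, no section sets site quotas, and the primary model does not need equal sites. Little should be made of the fact that the wording cannot be met literally.

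A reader might infer that the trial is underpowered because the site count is wrong. The documents do not support that: correcting five to six raises power. A reader might also ask whether the inflation should use the larger clusters that will actually be recruited. That question arises equally with five or six locations, and the answer depends on randomization taking place within locations and on location being in the model. It does not measure the discrepancy described here.

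**Conclusion.** The point holds as a minor inconsistency in an input to the calculation. The Sample Size Calculation section counts five participating locations where the rest of the article counts six, without explanation, and the published 157 very likely rests on the five. For six locations the same method gives 139 (144 with attrition as division by 0.8), and 157 to 158 patients give about 97% power (0.962 to 0.975 across the conventions tried). The 95% target is therefore kept.

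The contradiction is certain from the text. The sizes rest on rho = 0.5, sphericity, the interaction test and a cluster size taken from the uninflated sample.

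**What to change.** Redo the Sample Size Calculation section with six locations. Restate either the minimum sample or the power at 158, and give the assumed correlation between repeated measures and the way attrition was applied, so that the figure can be reproduced. If one facility does not count towards the calculation or the analysis, say so in the Abstract, Study Setting and Outcomes sections and give the reason.

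The cost is one recalculation and one corrected paragraph. The recruitment target and the analysis model need not change on this account.

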## Methods

### Design

We will perform a randomized controlled multicenter superiority trial with two parallel groups in the Netherlands. Both groups will receive standard IMPT, but the experimental group will be provided with the AGRIPPA app that they can access both during and after the treatment program. The nature of the intervention does not allow for masking the condition for health care providers or patients. The allocation ratio will be 1:1.

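### The 20% attrition correction appears to add 20% instead of dividing by 0.8, which would make the stated minimum of 157 about 7 patients too low (minor)

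*Protocol article*

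**What the plan says.** The Sample Size Calculation section of the protocol article rests on a "2-factor repeated-measures analysis of variance with within-factor time (5 levels) and between-factor treatment (2 levels) conditions" for the Pain Disability Index. It fixes the error rates ("We have set the α to .05, the power (1 – β) to .95") and takes an effect of f = 0.2. It then allows for clustering within 5 locations with a "formula for the variance inflation factor, assuming an intracorrelation coefficient of 0.2", and for dropout: "Furthermore, we corrected the analysis for an expected attrition of 20"%. The conclusion is "a minimum sample size of 157 participants, equally divided over 5 treatment locations, will be required".

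The section does not give the correlation between repeated measurements, the sample size before inflation, the value of the inflation factor, or the operation used for attrition. The Abstract plans to recruit 158.

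**The concern.** If a fraction d of patients is lost, the number to recruit is the number needed divided by (1 - d). Multiplying by (1 + d) falls short, because 1.2 × 0.8 = 0.96: after a 20% loss only 96% of the requirement is left. When the stated inputs are run through the usual routine, the published 157 appears at the multiplication by 1.2 and not at the division by 0.8.

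At stake is whether 157, presented as a minimum for 95% power, meets that target under the plan's own attrition rate.

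**Working it through.** **Inputs from the Sample Size Calculation:** 5 time levels (m = 5), 2 groups, alpha 0.05, power 0.95, f = 0.2, 5 locations, intracluster correlation 0.2, attrition 20%. The Primary Analysis section confirms that the time-by-treatment interaction is the effect of interest. The Design section gives 1:1 allocation.

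**Assumed, because not stated:** correlation between visits rho = 0.5 and sphericity (epsilon = 1), both customary defaults.

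**Step 1, base sample size.** Noncentral F test of the interaction, with lambda = f² × N × m / (1 - rho), df1 = 4, df2 = 4(N - 2).
- N = 48: lambda = 0.04 × 48 × 5 / 0.5 = 19.2, power 0.9516.
- N = 47: power 0.9470, below target.
- Base = 48.

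**Step 2, clustering.** Patients per location = 48 / 5 = 9.6. Inflation factor = 1 + (9.6 - 1) × 0.2 = 2.72. Then 48 × 2.72 = 130.56, so 131.

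**Step 3, attrition.**
- Multiply: 130.56 × 1.2 = 156.67, so 157. This is the published figure.
- Divide: 130.56 / 0.8 = 163.2, so 164.

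**Step 4, what remains after a 20% loss.**
- 157 × 0.8 = 125.6 and 158 × 0.8 = 126.4, both below 131.
- At the plan's factor of 2.72, 125.6 / 2.72 = 46.2 gives power 0.943, and 126.4 / 2.72 = 46.5 gives power 0.944.

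**Step 5, how far the match depends on rho.**

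| rho | Base | Factor | Product | × 1.2 | / 0.8 |
|---|---|---|---|---|---|
| 0.40 | 57 | 3.08 | 175.56 | 210.7 | 219.5 |
| 0.50 | 48 | 2.72 | 130.56 | 156.7 | 163.2 |
| 0.51 | 47 | 2.68 | 125.96 | 151.2 | 157.45 |
| 0.60 | 39 | 2.36 | 92.04 | 110.4 | 115.1 |

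On a grid of rho in steps of 0.002, values from 0.498 to 0.506 give a base of 48, and only × 1.2 reaches 157. Values from 0.508 to 0.516 give a base of 47, and then the correct division reaches 157.45. At the values in the table further from 0.5, neither operation comes near 157. The published total therefore points to rho close to 0.5, but does not by itself settle which operation was used.

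**The case against.** The strongest objection is that the alleged step is not in the text. The section says only that a correction was made, and that sentence is not wrong as written. This stands, and the multiplication by 1.2 must be called an inference.

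A second objection is that correct division can also give the published figure. With rho of about 0.51 the base is 47, and 125.96 / 0.8 = 157.45, which is 157 to the nearest integer and 158 rounded up, the recruitment figure in the Abstract. This stands too. It is the less natural route: it needs an unusual rho and an odd base that cannot be split 1:1, and rounding that base up to 48 brings back 163.2. The parity argument has limited force, however, because 157 is itself odd and does not divide equally over 5 locations.

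Third, counting only 126 patients treats dropouts as contributing nothing. The Missing Data section plans the multilevel analysis on incomplete data, so a patient lost partway keeps the earlier measurements in the model. The power loss above is therefore an upper limit on the plan's own chain.

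Fourth, the effect is small beside the uncertainty in f, rho and the intracluster correlation. That is right, and it sets the severity. It does not excuse a correction that fails to restore the number required.

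A reader might infer that 157 can be obtained only with the wrong operation, or that the trial will certainly fall short of 95% power for this reason. The document supports neither: it shows no operation and no rho, and its planned analysis uses partial data.

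**Conclusion.** The point holds as a probable arithmetic slip of minor weight. Under customary defaults the plan's inputs reproduce 157 with × 1.2, while the correct division gives 164. If × 1.2 was used, the minimum is 7 too low (6 against the planned 158). Power on the plan's own chain is then 94.3% with 157 or 94.4% with 158, against the 95% target and the 95.2% that a base of 48 gives, in the worst case where dropouts contribute nothing. The conclusion rests on rho = 0.5, sphericity and the plan's inflation factor of 2.72.

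That factor limits how far the corrected figures can be trusted. It uses 9.6 patients per location, whereas 157 / 5 is about 31. With the same formula at the evaluable number, 125.6 / 5 = 25.12 per location gives a factor of 5.824, an effective sample of 21.6 and a calculated power of 61.2%. Recruiting 164 changes that only to 61.5%. This is a separate matter from attrition and is not offered here as the trial's actual power. It shows that quoting 94.3% as a restated power would carry the 9.6 forward.

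**What to change.** In the Sample Size Calculation, state the assumed correlation between visits and the sphericity assumption, and give the chain in full: base number, inflation factor with the number per location behind it, number required after clustering, and number to recruit. Inflate for attrition by 1/(1 - 0.20).

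Then choose one of two courses:
- give the minimum as 164 on the plan's own chain (165 if it is to divide equally over 5 locations); or
- keep 157/158 and restate the power for about 126 evaluable patients, calculated with an inflation factor that matches the actual number per location.

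If another route led to 157, such as a correlation of about 0.51 with a base of 47, publishing those values settles the point.

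The cost is a few sentences and one corrected figure. The second course needs no extra patients; the first needs 6 more than the 158 planned (7 for the 165).
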